#### Community stakeholders

We will recruit six to nine community stakeholders for focus groups from two groups: (a) medical specialists (GPs, neurologists, rehabilitation specialists), (b) non-medical (local health authorities, NGOs, and social workers), who cooperate or partner with the selected MHCs.

### RE-AIM operationalization

Tables 1–5 shows the RE-AIM key indicators and data sources we will use to address the RE-AIM dimensions. We will assess the five dimensions of the RE-AIM framework across three levels (patient, provider, and community) as follows:

1 Reach

Quantitative assessment- patient levelWe will capture the number, proportion, demographics, clinical characteristics, and referral sources of patients receiving care at MHCs.Qualitative assessment- patient levelIt will complement the quantitative data to identify barriers and facilitators to accessing services.

2 Effectiveness

Quantitative assessment - patient levelWe will assess patient symptoms and severity of specific mental health conditions using standardized questionnaires previously applied in the MAP studies, covering Post-Traumatic Stress Disorder (PTSD), depression, somatic distress syndrome, anxiety, and alcohol use, in addition to health-related quality of life and mental well-being. (24, 25)Qualitative assessment - patient levelTo understand patient perspectives on perceived benefits, harms, and contextual explanations for outcomes.

3 Adoption

Quantitative assessment- provider levelWe will capture the characteristics of all eight MHCs and their affiliated providers to quantify the extent and representativeness of adoption. We will assess factors influencing adoption. We will also measure work-and non-work-related health factors to control for external confounders in this war-affected context.Qualitative assessment- providers and community levelsWe will examine providers’ experiences and perceptions of the MHC model, alongside how mental health services integrate with primary care and the wider community.

4 Implementation

Quantitative assessment- provider levelWe will evaluate the determinants and consequences of organizational readiness for implementation.Qualitative assessment- provider and community levelsIn the absence of a standardized protocol for implementation, fidelity will be explored qualitatively. We will capture operational processes, resource allocation, and center-specific barriers and enablers to implementation. In addition to that, collaboration with the community. We will share the findings with the MH4U team, providers, and community stakeholders to facilitate the translation of evidence into actionable insights.

5 Maintenance

Quantitative and qualitative assessment- patient, provider, and community levelsIt will be assessed as part of a future follow-up phase ≥ six months after the second phase. We will examine the sustained impact and institutionalization of MHCs, as well as disseminate the findings.

**Table 1 tab1:** Reach key indicators, data sources, and target group.

Key indicators	Data source	Target group (level)
% of eligible community members who received at least one MHC service vs. MAP studies	Center records	Patients
Representatives of patients: Distribution of demographic and clinical characteristics vs. MAP studies % of patients referred through each source (self, GP, etc.)	Baseline assessment questionnaire	Patients
Key barriers and facilitators to access the service	Interviews	Patients

**Table 2 tab2:** Effectiveness key indicators, data sources, and target group.

Key indicators	Data source	Target group (level)
Mean change in patients outcome over time	Posttraumatic Stress Disorder Checklist (PCL-5), Patient Health Questionnaire (PHQ-9), PHQ-15, Generalized Anxiety Disorder 7 (GAD-7), the Alcohol Use Disorders Identification Test (AUDIT), European Quality of Life 5 Dimensions (EQ-5D-5L) and the visual analogue scale (EQ-VAS), and mental wellbeing by Short Warwick-Edinburgh Mental Wellbeing Scale (SWEMWBS) (22, 35–40).	Patients
Therapeutic alliance	Working Alliance Inventory – Short Revised (WAI-SR) (41).	Patients
Attrition rate: % of patients lost to follow-up Differential retention on demographics and clinical characteristics between completers and dropouts	Center records	Patients
Themes of perceived benefit and challenge	Interviews	Patients

**Table 3 tab3:** Adoption key indicators, data sources, and target group.

Key indicators	Data source	Target group (level)
Characteristics of participated MHCs and providers MHC rate of diagnosis and service provision MHC rate of referred patient’s uptake of one or more sessions Center level variability in adoption	Center records	Providers Centers
Team functioning	Team Development Measure (TDM) (42)	Providers
Mental health stigma among providers	Mental Illness Clinicians’ Attitudes Scale (MICA-4) (43)	Providers
Work-related wellbeing and staff health	Copenhagen Psychosocial Questionnaire (COPSOQ-III), Burnout Assessment Tool (BAT), General Health Questionnaire (GHQ-12) and Perceived stress scale (PSS-10) (44–48)	Providers
Themes on organizational barriers and facilitators to adoption	Interviews	Providers
Perceptions and experiences of MHC model in the community	Focus groups	Community stakeholders

**Table 4 tab4:** Implementation key indicators, data sources, and target group.

Key indicators	Data source	Target group (level)
% of services delivered as planned Consistence of referral over time per MHC	Center records	Providers Centers
organizational readiness	Organizational Readiness for Implementing Change (ORIC) (49)	Providers
Themes describing core implementation components of fidelity, facilitators, and barriers	Interviews	Directors
Themes capturing real world implementation in practice	Interviews	Providers
Quality and effectiveness of collaboration in implementation	Focus groups	Community stakeholders
Documentation and utilization of feedback and iterative learning from workshops	Workshops	Providers, MH4U team and community stakeholders

**Table 5 tab5:** Maintenance key indicators, data sources, and target group.

Key indicators	Data source	Target group (level)
Long-term patient mental health outcomes	PCL-5, PHQ-9, PHQ-15, GAD-7, AUDIT, EQ-5D EQ-VAS and SWEMWBS	Patients
Robustness of long-term effects across patient subgroups Long-term attrition and differential retention by patient characteristics or clinical condition	Center records	Patients
Center-level adaptations post-project Organizational-level sustainability	Interviews	Providers
	Focus groups	Community stakeholders
Engagement in planning and implementing long-term sustainability of MHC practices	Workshops	Providers, MH4U team and community stakeholders

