### Participants

#### Patients

##### Intervention cohort

The inclusion criteria are: (a) Adults (≥18 years), (b) have received one to three treatment sessions at one of the participating MHCs, and (c) have provided informed consent. Patients will be excluded if they have only received an emergency session or if a treating psychiatrist determines they have severe cognitive dysfunction or an acute mental health condition that would impair their ability to participate.

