##### Sample size calculation

We will recruit a prospective longitudinal cohort via a non-probability sampling technique. Each participating MHC representing a cluster because patient outcomes are expected to be correlated within centers due to shared staff, resources and local community. Approximately 400 patients for the 8 MHCs (targeting ~50 per MHC) will be enrolled in the quantitative assessment. The primary outcome is the change in depressive symptoms measured by the Patient Health Questionnaire-9 (PHQ-9) scale from baseline to follow up 4 (approximately one year) (22).

We estimated the variance of the PHQ-9 change score empirically as:

$$\mathrm{Var}\;(\Delta )=\sigma_{b}^{2}+\sigma_{f}^{2}-2r\sigma_{b}\sigma_{f}\;$$

Where 
$\sigma_{b}=5.97$
 and 
$\sigma_{f}=5.50$
 are the baseline and follow-up 4 standard deviations (SDs), respectively, and 
r=0.546
 is the within-person correlation. Substituting these values gives 
Var(Δ)≈30.0
, yielding 
${\mathrm{SD}}_{\Delta }\approx 5.48$
.

We account for clustering between MHCs using design effect,

DE=1+(m−1)ICC

Where m = 50 is the average cluster size and ICC is the intraclass correlation. Under this framework (two-sided significance level 5 and 80% power), the minimum detectable difference in difference (DiD) effect in PHQ-9 points is approximately 0.94, 1.08, and 1.43 for ICC = 0.01, 0.02, and 0.05, respectively.

We will invite a subsample from the quantitative cohort of patients to interviews through a purposive sampling strategy (23). Patients will be selected with varying treatment exposure (≥1 session) to capture diverse treatment experiences and outcomes. The qualitative sample size will be guided by content saturation.

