##### Patient

Eligible patients for the cohort will receive a flyer during their regular visit at the MHC, containing essential study information with a QR code directing them to a Research Electronic Data Capture (REDCap) registration form (26, 27). We will assess the eligibility based on the submitted registration data. Eligible participants will then be contacted via their preferred way of communication and provided with a personalized link to provide informed consent and complete the self-administered quantitative assessment instruments. Follow-up assessments will be conducted via REDCap at three- and six-month intervals after baseline.

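### The Reach row on patient characteristics and referral sources is defined for all MHC patients but taken from a questionnaire that only self-registered study participants complete

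*Protocol article*

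**What the plan says.** Under RE-AIM operationalization, the patient-level quantitative part of Reach is to capture the number and proportion of patients, and the "demographics, clinical characteristics, and referral sources of patients receiving care at MHCs". The population is the centers' patients, with no restriction to study participants.

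Table 1 then assigns data sources. Its first row, the proportion of eligible community members served, uses center records. Its second row holds two indicators, "Representatives of patients: Distribution of demographic and clinical characteristics vs. MAP studies" and the percentage of patients arriving by each referral route. The source given for both is "Baseline assessment questionnaire".

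How someone comes to complete that questionnaire is set out elsewhere:

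- Sample size calculation: "We will recruit a prospective longitudinal cohort via a non-probability sampling technique", with about 400 patients in total and about 50 per MHC.
- Intervention cohort: adults who "have received one to three treatment sessions at one of the participating MHCs". Patients seen only for an emergency session are excluded. So are those in whom the treating psychiatrist finds severe cognitive dysfunction or an acute condition that would impair participation.
- Quantitative data collection, Patient: a flyer is handed out at a regular visit, "containing essential study information with a QR code directing them to a Research Electronic Data Capture (REDCap) registration form". Those found eligible are then contacted and "provided with a personalized link to provide informed consent and complete the self-administered quantitative assessment instruments".

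The comparator, MAP, is described as a probability-based sample of the general population.

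**The concern.** The stated population and the stated data source do not match. A row meant to show whom the centers reach would show who joined the study.

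Two uses of the row are affected. The first is the comparison with MAP. Any gap between the cohort and a probability sample of the population reflects both who attends an MHC and who, among attenders, is eligible and registers. The row cannot separate the two. The second is the learning-health-system plan, which will examine changes in RE-AIM indicators, Reach included, between the first phases and the follow-up phase as possible effects of feedback. A change in who registers would look the same as a change in who is reached.

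The aims tie these results to refinement and national scale-up, so a misread Reach row could point policy towards the wrong under-served groups.

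**Working it through.** **1. Who can and cannot appear in the row.** Setting the Reach definition beside the recruitment text:

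| Patients the MHCs reach | Can appear in the second row of Table 1? |
|---|---|
| Emergency session only | No, excluded |
| More than three sessions at recruitment | No, outside the entry window |
| Severe cognitive dysfunction, or acute condition impairing participation (psychiatrist's judgement) | No, excluded |
| Eligible, but do not register or consent online | No, no questionnaire |
| Eligible, registered, consented and completed | Yes |

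The first three lines follow from the eligibility rules. The fourth depends on a participation rate that the article does not give.

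**2. Whether any stated method repairs it.**

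- Inverse probability of censoring weighting is for loss to follow-up, after entry.
- Inverse probability weighting balances MHC patients against MAP for outcome comparisons. It does not model entry into the cohort, and for Reach it would remove the very differences the row should display.
- Reminders and telephone contact are for participants who stop responding, not for patients who never registered.
- The Limitations section does not mention participation.

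**3. Reproducing the plan's own figure, to borrow its design effect.** Inputs from Sample size calculation: SDs 5.97 and 5.50, r = 0.546, m = 50, n = 400, two-sided 5%, 80% power.

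- Var(Δ) = 5.97² + 5.50² − 2 × 0.546 × 5.97 × 5.50 = 30.04, so SD = 5.48.
- DE = 1 + 49 × ICC = 1.49, 1.98 and 3.45 for ICC 0.01, 0.02 and 0.05.
- Detectable effect = (1.960 + 0.842) × 5.48 × √(DE/400) = 0.94, 1.08 and 1.43, as the plan states.

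The present point does not depend on these effects. Only DE is carried forward. Using it for a proportion is an assumption, since the plan gives these ICCs for PHQ-9.

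**4. Illustration on assumed rates.** Let p be a group's true share of MHC patients and R its registration rate relative to other patients. Then

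observed share = pR / (pR + 1 − p).

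With p = 0.30 (assumed):

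- R = 1: 0.30 / (0.30 + 0.70) = 30%, shift 0.
- R = 1/2: 0.15 / (0.15 + 0.70) = 17.6%, shift 12.4 points.
- R = 1/3: 0.10 / (0.10 + 0.70) = 12.5%, shift 17.5 points.

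Sampling error for p = 0.30, n = 400:

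- Unclustered: √(0.30 × 0.70 / 400) = 2.3 points.
- Clustered: 2.29 × √1.49 = 2.8 points (ICC 0.01) to 2.29 × √3.45 = 4.3 points (ICC 0.05).

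The shift can also go upward. With a true self-referred share of 40% (assumed) and R = 1.5, the observed share is 0.60 / (0.60 + 0.60) = 50%.

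**The case against.** Several counter-arguments have weight.

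- **Direction is unknown.** A reader might infer that older, less digital or more severely ill patients are under-represented by construction. The document does not support that. Only the groups removed by the eligibility rules are missing by construction. The flyer is handed over in person and no registration rate is given. Contact by the preferred route helps, but only after registration.
- **The exclusion is narrow.** It would be wrong to read it as removing everyone with an acute condition or any cognitive dysfunction. It requires severe dysfunction, or an acute condition that impairs participation, as judged by a psychiatrist.
- **The size is hypothetical.** A fixed multiple of bias over sampling error cannot be claimed. With R = 1 there is no bias from registration, and an unclustered standard error of 2.3 points is too small for a plan that treats centers as clusters.
- **Part of the row needs the questionnaire.** The clinical comparison with MAP relies on scales already used in MAP, and the document does not say that center records hold them. The criticism is strongest for demographics and referral source.
- **Other record-based indicators exist.** Diagnosis rates and referral uptake (Table 3) and referral consistency (Table 4) come from center records. They give some information not confined to respondents, but they do not replace the characteristics of the people reached.
- **Non-probability sampling is openly stated.** That discloses the cohort's nature. It does not make the cohort a valid source for a row about all patients.

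These points limit the claim. They do not remove the mismatch between population and source.

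**Conclusion.** The point holds as a mismatch between the population in the Reach definition and the data source in the second row of Table 1. Followed as written, the plan would describe study respondents. Some reached patients are left out by rule. Others may be left out through differential registration, and no stated method addresses either.

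The size cannot be computed from the document. Under the assumed 30% share, the shift runs from 0 (equal registration) to 12.4 points (half) and 17.5 points (one third), against a clustered standard error of 2.8 to 4.3 points. Marked differential registration would therefore outweigh random error, while equal registration would add no bias of its own. This rests on the assumed share and rates, and on the plan's m = 50 and ICC 0.01 to 0.05 applying to a proportion.

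The scope is limited. The first Reach row uses center records and is unaffected. This point does not bear on the definition of the primary PHQ-9 outcome. A reader might infer that the whole second row should leave the questionnaire, but the symptom scales compared with MAP have no other stated source.

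**What to change.** In Table 1, split the second row by source:

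- Take age, sex, diagnosis group and referral source from center records of all MHC patients in the period, wherever the records hold them.
- Keep the baseline questionnaire for the symptom scales compared with MAP and for items the records lack.
- Tabulate cohort against all-patient characteristics for each center.
- When the cohort is used to describe Reach, weight it to the record margins.
- Label any item that remains questionnaire-only as describing the study cohort.

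The cost is a change of wording in Table 1, a request for aggregate tables, and a modest weighting step. Center records are already to be obtained for 2025. They already serve the first Reach row, the differential-retention indicator on demographic and clinical characteristics in Table 2, and the diagnosis and referral indicators in Tables 3 and 4. A comparison of Reach between phases would need the same tables for the later period.

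The downside is that records may hold fewer variables than the questionnaire. The article does not confirm that age, sex, diagnosis and referral source are held for all patients in usable form, so this should be checked with the centers first. Where they are not held, the relabelling still applies.

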### LHS operationalization

The LHS will be operationalized through staged feedback loops aligned with our study phases to MH4U coordination, MHC leadership and community stakeholders.

We will provide direct feedback following the initial and scale up phases and then again after the follow up phase.We will conduct workshops after the scale up phase to share our findings and reflect on implementation challenges and adaptation priorities in real life situation.We will hold a second round of workshops following the follow up phase to present our longitudinal findings, assess sustainability and adaptation after our feedback and support national expansion of the MHC model.

Learning will be operationalized as documented adaptations linked to evaluation findings. Moreover, changes in key RE-AIM indicators between first phases and follow up phase will be examined to assess whether feedback-informed adaptations are associated with improvements in Reach, Effectiveness, Adoption, or Implementation. Workshop documentation will further explore provider and stakeholder perceptions of how feedback influenced decision-making and practice change.

### Data collection methods

All study materials not originally available in Ukrainian underwent forward and backward translation to ensure linguistic and conceptual equivalence. Quantitative validated Ukrainian instruments will be used when available; otherwise, translated tools were pretested, piloted, and adapted as needed and reviewed by the study team at Sumy State University in Ukraine. In addition, we will assess internal consistency reliability and construct validity, as the range of instruments used allows. Then, we will examine indices such as Cronbach’s alpha and compare expected and observed correlations. We will compare these results with published psychometric validations from other countries.

#### Quantitative data collection

##### MHCs

Annual center administrative records, collected routinely at the end of each calendar year, will be obtained retrospectively in January 2026 to capture data from 2025.

##### Patient

Eligible patients for the cohort will receive a flyer during their regular visit at the MHC, containing essential study information with a QR code directing them to a Research Electronic Data Capture (REDCap) registration form (26, 27). We will assess the eligibility based on the submitted registration data. Eligible participants will then be contacted via their preferred way of communication and provided with a personalized link to provide informed consent and complete the self-administered quantitative assessment instruments. Follow-up assessments will be conducted via REDCap at three- and six-month intervals after baseline.

##### Provider

All providers affiliated with the participating MHCs and MHCs that are not supported by MH4U will be invited to participate through a study summary along with a personalized Redcap link, through which they can provide informed consent and complete the quantitative assessment instruments. All providers will be invited again to complete the same set of instruments at the follow-up, which will be approximately one year from the baseline.

#### Qualitative data collection

##### Patient

We developed interview guides for patients structured around the concept of the “patient journey,” and designed to map the individual’s pathway into, through, and beyond the MHCs. We will conduct the interviews by telephone.

##### Provider

We developed interview guides for providers, and they will be interviewed in person during site visits by the Sumy study team.

##### Interview piloting and refinement

Interview guides were piloted in person at Polyclinic No. 1 in Lviv with twelve patients and three providers through in-person interviews to ensure clarity, cultural appropriateness, and alignment with the study objectives. We documented key findings and observational insights. Based on this report, the guides were iteratively refined. The interview lasted approximately 60 min for both patients and providers.

##### Community stakeholders

We developed the focus group guides. One focus group for medical and one for non-medical community stakeholders will be conducted in person per oblast. In Lviv, where the number of MHCs is relatively large, a total of four focus groups will be conducted to ensure representation while maintaining manageable group sizes and discussion dynamics.

##### Non-response and attrition management

We will employ multiple engagement strategies. If a participant does not respond within ten days, we will send a reminder. We will monitor participation patterns and initiate direct follow-up by telephone for participants who remain unresponsive. When available, reasons for non-response or dropout will be recorded.

